### Study sites

The study is being executed in the National Dental PBRN, a collective network of dental practices that includes private and group practices, public health clinics, community health centers and Federal Qualified Health Centers (FQHCs), academic institutional settings, and special patient population [32]. Since its inception in 2005, the Network has matured into a national network with coverage in urban and rural areas and participation by general dentists, dental specialists, and dental hygienists [33]. The Network is interested in increasing the study and use of HIT to collect PROs within its clinics. It is highly productive, with 19,827 practitioners participating in one or more Network studies [33], and 762 practitioners actively being part of at least one clinical study [34, 35]. The Network has been involved in 58 studies. Practice-based research promotes not only the collection of data at the provider and patient levels but also allows the gathering of patient perspectives before, during, or after the visit. The Network’s infrastructure has matured through various management initiatives into a nimble yet continuous, quality-improvement conscientious network [36]. It is rapidly moving toward achieving the vision of a Learning Health System [37]. Hence, this environment is ideal for developing a practical, focused post-operative pain management study. The six Network geographic regions in the US will be informed of the study protocol and opportunity to participate. We anticipate that all Network practitioners stratified by state, urban/rural, and practice size, will be eligible to participate; between 150 to 215 Network practitioners will be recruited.

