3. Patient screening and enrollment	Each participating office will decide if practitioners or office staff will screen/enroll patients in the study. The office staff who enroll patients will need to have successfully completed appropriate training. Each participating office will maintain a log of screened and enrolled subjects. On a weekly basis, office staff will record their summary screening/enrollment information in the electronic data capture (EDC) system. Practitioners will enroll patients via a consecutive process that best suits their practice situation, i.e., they will approach any patient who may meet the inclusion criteria during the days and/or times when the office is participating in research activities.
4. FollowApp.Care platform activation	Enrolled practitioners will individually be able to request their FollowApp.Care notification preferences, for example, they can choose to receive notifications by email or text. Notifications will be sent to practitioners based on predefined thresholds defined in the manual of procedures (MOP).
5. Patient evaluation (Usability questionnaire)	Patients will complete a Usability survey (SUS) on day 23 using the FollowApp.Care platform.
6. Practitioner evaluation (debriefing/interview session and UTAUT questionnaire)	Once the patient component of the study has been concluded, we will administer the UTAUT Questionnaire to all participating practitioners to assess their perceived usefulness and perceived ease of use of FollowApp.Care as predictors of their usage behavior. Thereafter, we will conduct virtual debriefing/interviews with up to 45 purposefully selected practitioners to qualitatively evaluate their experiences with using FollowApp.Care for managing their patients’ post-op pain. These debriefing/interview discussions will be audiotaped and transcribed for analysis.

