### Sample size

A minimum of 150 and up to 215 dental providers will be recruited, and each provider will be expected to enroll an average of 21 patients for a total of 3147. Assuming a 40% missing data rate among enrolled patients throughout the duration of the study, there will be 1888 patients remaining. This includes patient non-response rates as well as item non-response rates for the outcome of interest during the study period. Given a sample of 1888, the GLMM model for repeated measures will be able to detect a 20% reduction in pain intensity between procedure groups over time with 80.0% power. The minimum sample size was derived by the “longpower” sample package in the R statistical computing environment.

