### Statistical analysis

Standard descriptive statistics will be used to describe both patient and practitioners’ characteristics using 5 data capture methods: 1) the SUS questionnaire, 2) the mHealth Questionnaire distributed on pre-specified days post procedure, 3) the UTAUT questionnaire, 4) the debriefing/interviews, 5) and the practitioner eCRF. Summary statistics such as means, medians, and ranges will be produced for all measured continuous variables. Frequencies and percent contributions will be computed for all categorical and ordinal variables. Graphical methods like X-charts will examine distributions over time and identify potential, influential time points. The balance of baseline characteristics and measures between groups will be compared using appropriate tests, including chi-squared tests, student t-tests, and Wilcoxon rank-sum tests.

A challenge for this non-randomized study is confounders – pre-existing variables that affect the outcomes and differ between the treatment groups. In order to reduce bias, potential confounders variables will be adjusted in regression models for the analysis. Once participants discontinue the study, they will not be contacted and will not be replaced as the power calculation has accounted for them. If the discontinuation rate is high, the study team PIs will discuss how to proceed with the Network and NIDCR. We will create a missing category for all missing data and assess the need for any imputation methods.

We will estimate the difference in intensity, pain interference, and patient satisfaction dependent on the treatment type. The relative risk (RR) will be the measure of association reported along with 95% confidence intervals. Pain, interference, and satisfaction at the end of the study will be compared among the treatment categories. To model the differential treatment (CDT Grouping) effect on patients’ pain intensity, interference, and satisfaction, on, we will use GLMMs using a Poisson link. Models will include time, treatment type, age, gender, race/ethnicity, medications, and no medication methods as fixed effects. In addition, dentist and Network regions will be included as random effects in the models to account for correlations within clusters.

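### Clustering is modelled by dentist and region only; if offices enrol several dentists and procedure type differs between practices, standard errors for procedure contrasts can be too small

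*Protocol article*

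**What the plan says.** The Statistical analysis section compares pain intensity, interference and satisfaction between procedure groups with Poisson GLMMs. It lists the fixed effects and then says that "dentist and Network regions will be included as random effects in the models to account for correlations within clusters". Practice or office appears neither as a random nor as a fixed effect.

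Under Study sites, the Network is described as "a collective network of dental practices that includes private and group practices, public health clinics, community health centers", and academic settings are also listed. Recruitment there is counted in practitioners: "between 150 to 215 Network practitioners will be recruited". No number of practices and no cap on dentists per practice is given, and practice size is named as a stratification variable. On regions, the same section says "The six Network geographic regions in the US will be informed of the study protocol and opportunity to participate".

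Table 3, under Study activities and data collection, places enrolment at the office: "Each participating office will decide if practitioners or office staff will screen/enroll patients in the study". Each office also keeps the screening log, and patients are approached at times when the office is taking part in research. The FollowApp.Care section describes a Center level in the platform's access permissions.

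**The concern.** Patients of different dentists in one office share staff, catchment and the way they were selected. If their outcomes are correlated through the office, a model with dentist and region effects only leaves that correlation out. Region cannot stand in for it: with six regions and 150 to 215 dentists, a region holds on average 150/6 = 25 to 215/6 = 36 dentists.

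The primary comparisons (Hypotheses 1 to 3) are between procedure groups. An office that mainly does one kind of procedure, such as a specialist practice, would contribute mostly to one group, and the unmodelled correlation would then fall on the comparison of interest. Confidence intervals would be too narrow, and tests at the nominal 0.05 would reject too often.

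**Working it through.** **The plan's own figures.** The Sample size section says that "each provider will be expected to enroll an average of 21 patients for a total of 3147", and then: "Assuming a 40% missing data rate among enrolled patients throughout the duration of the study, there will be 1888 patients remaining". Both reproduce: 150 × 21 = 3150, close to 3147, and 3147 × 0.60 = 1888.2. Analysed patients per dentist are 1888/150 = 12.6 at the minimum number of dentists and 1888/215 = 8.8 at the maximum. The 80% power cannot be reproduced, because the article gives no SD, within-patient correlation, group sizes or intraclass correlation. It is not needed here.

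**Assumed inputs, not in the documents.** Let m be the number of enrolled dentists per practice. The total between-dentist intraclass correlation (ICC) is 0.05 or 0.10, with half of it shared within practice. There is one outcome value per patient, the test is two-sided at 0.05, and the contrast lies wholly between practices.

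**Formulas.** A dentist-only model absorbs the practice variance into the dentist variance. With n analysed patients per dentist:

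- r = practice variance / (ICC + (1 − ICC)/n)
- true variance / model variance = 1 + (m − 1)r
- SE ratio (model/true) = 1/√(1 + (m − 1)r)
- true type I error = 2(1 − Φ(1.96 × SE ratio))

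**Numbers in, n = 12.6.** At ICC 0.05, r = 0.025/(0.05 + 0.95/12.6) = 0.199. At ICC 0.10, r = 0.05/(0.10 + 0.90/12.6) = 0.292.

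| Dentists per practice | ICC 0.05: SE ratio, type I error | ICC 0.10: SE ratio, type I error |
|---|---|---|
| 1 | 1.00, 5.0% | 1.00, 5.0% |
| 1.2 (average) | 0.98, 5.5% | 0.97, 5.7% |
| 2 | 0.91, 7.3% | 0.88, 8.5% |
| 3 | 0.85, 9.7% | 0.80, 11.9% |

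The 1.2 row treats the average as a common size. If instead one practice in five enrols two dentists and the rest one, the dentist-weighted size is (0.8 × 1 + 0.2 × 4)/1.2 = 1.33. The variance factor at ICC 0.05 is then 1 + 0.33 × 0.199 = 1.066, and the type I error is 5.8%.

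**Sensitivity.** With n = 8.8, the type I error at ICC 0.05 is 6.9% (two dentists) and 8.8% (three); at ICC 0.10 it is 7.9% and 10.9%. For two dentists per practice, over ICC 0.02 to 0.10, shared fraction 50% to 100% and n from 8.8 to 12.6, it runs from 5.9% to 11.9%.

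**When procedure also varies within dentist.** An exact generalised least squares calculation used a linear analogue with 144 dentists, 12 patients each, ICC 0.05 and half of it at practice level.

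| Share of patients whose procedure is unrelated to practice | SE ratio, type I error (m = 2) | SE ratio, type I error (m = 3) |
|---|---|---|
| 0% (wholly between practices) | 0.92, 7.3% | 0.85, 9.6% |
| 25% | 0.96, 6.0% | 0.92, 7.2% |
| 50% | 0.98, 5.4% | 0.97, 5.7% |
| 100% (wholly within dentist) | 1.00, 5.0% | 1.00, 5.0% |

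The first row agrees with the closed formula. These are linear-model results and serve as a guide to the Poisson GLMM.

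**The case against.** The strongest reply is that the consequence needs three things together: several enrolled dentists per practice, practice variance beyond that of the dentist, and procedure groups that differ between practices. The article quantifies none of them. Recruitment is by practitioner, and one dentist per practice fits the text. The mix of settings describes the whole Network, not the enrolled sample. A dentist qualifies with at least one listed procedure a week across endodontic, periodontal, surgical and implant codes, and general dentists take part, so one dentist may well contribute to several groups. If procedure differs between dentists inside one office, the practice effect cancels and the dentist-only model errs in the safe direction. All of this stands, and it is why the point is conditional.

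It can also be said that a further nesting level is detail for the analysis plan. That stands in part: nothing in the article prevents the SAP, which is not at hand, from adding one. But the article does not leave the clustering levels open. It names them, and practice is not among them.

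Two stronger readings are tempting. One is that the planned standard errors are too small as a matter of fact, with type I error as high as 18.3%. That figure follows from the same formula at ICC 0.10 with five enrolled dentists in every practice (factor 1 + 4 × 0.292 = 2.17) and a contrast wholly between practices; the documents support none of these conditions. The other is that treating six regions as random is itself an error. Six levels estimate a variance weakly, but fixed or random is a matter of preference here, and no harm to a procedure contrast follows from anything in the article.

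**Conclusion.** The point holds as a conditional weakness in a stated model. The plan recognises clustering but names no level for the office, the unit through which patients are enrolled. Inflation of the size shown for two or three dentists per practice is an upper case for those values of the ICC and shared fraction, because it takes the contrast as lying wholly between practices. It falls to under 6% when half of the patients' procedures are unrelated to practice, or when practices average about 1.2 enrolled dentists. It is nil with one dentist per practice or with procedure varying wholly within dentist. All ICCs, the shared fraction and the number of dentists per practice are assumptions. The change is worth making because it is cheap and the affected contrasts are primary, not because the documents show that inflation will occur.

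**What to change.** In the GLMMs of the Statistical analysis section, add practice (office) as a random effect above dentist, so that patients are nested in dentists and dentists in practices. Alternatively, keep the present terms and use standard errors clustered by practice. If the study will enrol only one dentist per practice, saying so would settle the matter without any change to the model. The region term can stay as it is.

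The cost is a practice identifier in the analysis data. The article does not list one among the practitioner variables, and it does not say that the platform's Centers correspond to practices, so its availability should be confirmed. Some confidence intervals will widen.

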## Discussion

In our pilot study (AHRQ 1U18HS026135), we successfully explored how an innovative mobile health intervention (FollowApp.Care®) could optimize the quality of acute post-op dental pain management by collecting PRO data from patients after dental procedures. However, it also taught us a number of implementation barriers. Some of these barriers are not new to those collecting PRO data, including difficulties with optimizing workflows and minimizing logistical burdens, further exacerbated by the expanded precautionary settings during COVID; data management in light of staff turnover; and staff training and providers [30, 31]. Barriers specific to implementing dental PROs using mHealth included making sure that providers see and act upon alerts timely; a hybrid approach to recruitment of patients due to the COVID environment; inaccurate phone numbers, and phone carrier contractual issues that prevented text messaging.

These barriers can substantially hamper the implementation of PROs by the general dentist, to the detriment of advancing patient-centered care in the dental arena. In the POPS (**P**ost-**O**perative **P**ain **S**tudy) trial (UH3DE029158, Understanding Pain after Dental Procedures), we seek to address the gap in knowledge by implementing an existing mHealth technology (FollowApp.Care) in the dental office setting. Through the FollowApp.Care platform, we will actively track pain and other complications following dental procedures. We expect to identify specific pain experiences associated with surgical dental procedures promptly and precisely. We will also collect information about pain management strategies and medications recommended by the practitioner and utilized by the patient. The results of this study will provide insight into pain and other postoperative complications experienced by patients through approximately 3 weeks following common dental procedures. We will also be able to gauge to what extent practitioners are interested in adopting mHealth technology. We will also learn how patients like to be engaged with text messaging to report post-operative pain and complications.

## Limitation

This observational study offers insight into the distribution of patient-reported outcomes, while also capturing information on strategies used by practitioners for pain management. However, a challenge for this non-randomized study is confounders – pre-existing variables that affect the outcomes and differ between the treatment groups. In order to reduce bias, potential confounders variables will be adjusted for in regression models for the analysis. We will create a missing category for all missing data and assess the need for any imputation methods.

## Data Availability

Not applicable.

## Abbreviations

ADA: American Dental Association (ADA)
AAOMS: American Association of Oral and Maxillofacial Surgeons
AAE: American Association of Endodontists
API: Application program interface
APS-POQ-R: American Pain Society Patient Outcome Questionnaire
CDT: Code on Dental Procedures and Nomenclature (CDT Code)
CFA: Confirmatory factor analysis
cIRB: Central IRB
EDC: Electronic data capture system
GCP: Good clinical practice
GLMM: Generalized linear mixed model
HIT: Health information technology
IT: Information Technology
IR: Immediate-release
IRB: Institutional Review Board
mHealth: Mobile health
MOP: Manual of Procedures
PROs: Patient-reported outcomes (PROs)
OMFS: Oral and Maxillofacial Surgery
PROMIS: Patient RepoPatient-Reportedasurement Information System
RR: Relative Risk
SUS: System Usability Score
UAB: University of Alabama
US: United States
